### Smartwatch sub-study data collection

Smartwatches can passively and continuously monitor a person’s routine behavior, including activity level and social interaction in real-time, using EMA responses and objective measurements, e.g. latitude, longitude. Their use in this study will provide a mechanism to model human behavior in naturalistic settings and to map digital behavior markers onto predicted clinical measures. Studying real-time data provides more detailed insights into immediate changes to behaviors and mood that occur when encountering low air quality or distressed environments and how this translates to cognitive performance.

Collected smartwatch sensor data will include accelerometer, gyroscope, heart rate, oxygen saturation, respiration rate, and location. The custom smartwatch app queries participants 4 times a day at random times during waking hours (between 8am and 8pm with a minimum one-hour gap between queries). If a user does not respond within 2 minutes, the app will repeat the query after a five-minute pause. If the user still does not respond, the app will wait until the next query time to interact with the user. The watch provides a notification in the late evening to charge the watch and in the early morning (if still on the charger) to put on the watch. We will synchronize smartwatch behavior markers and sensed location data with air quality readings and built and social environment data. Research Assistants will provide weekly check-in support for smartwatch participants.

EMA = Ecological Momentary Assessment

We will then employ joint inference machine learning to predict each target variable from the combined set of features. We will report correlations between automatically derived and self-reported measures of activity and SI. To assist in ensuring a minimum 80% adherence rate, our software will alert RAs if a lapse of ≥ 1 day in data collection occurs. The RA will check in with participants each week, as well as times these lapses are detected, to answer questions about using the smartwatches.

The following statistics are calculated for each data source by day and overall: mean, standard deviation, min, max, power, zero crossing, skewness, kurtosis, peaks, autocorrelation. Data sources include the raw sensor values collected by the smartwatch. They also include the following digital markers:

Activity level, total time for sleep, eat, work, exercise, relax, errands, travel, walk, run, lie down, based on automatically recognized activitiesAudio journal sound features: pitch, rate, intensity, spectrum, formants, harmonicity, MFCC, pauses and duration, speech beats/minute, FOAudio journal text features (based on speech-to-text conversion): unique phrases/words, characters/word, SMOG, named entities, sentiment/mood markers, LIWC, TF-IDF, word embeddings, LDALocation: distance/bearing from home, distance travelled, durations at frequented locations, transitions, air quality and temperatureN-back: score statistics, score slope and y-intercept, convergence rate, convergence meanEMA: response values, response rate

### Data management plan and security

A Data Safety Management Plan is in effect and overseen by the Florida Atlantic University Data Safety Management Officer. To minimize risk of breach of confidentiality, all informed consents and study materials will be entered on encrypted, password-protected computers using an electronic REDCap database. This database will be accessible only to the authorized research team members and will be stored on secure servers at Florida Atlantic University. A dual authentication and University-issued password is required to access this database. Using brief, efficient, and culturally sensitive methods for measurement, we will take every precaution to ensure confidentiality.

### Safety considerations

A Data Safety Monitoring Board is not required for this observational cohort study. There are minimal risks associated with study measures and assessments. Data collection occurs during a one-on-one visit between the community research assistant (CRA) and participant in private settings. Embarrassment about performance, fatigue, or stress from discussion about psychosocial situations may occur. The experienced research team of healthcare professionals is prepared to deal with participant concerns and make referrals if needed. In the unlikely event that any adverse event does occur, such as a physical fall or breach of confidentiality, the FAU Institutional Review Board will be notified.

### Sample size/power

#### Sample size calculations for full sample

Sample size estimates were made to attain .8 power for Aims 1 and 2. The intraclass correlation was assumed to be .05 based on the cluster of neighborhoods within rural communities. For Aim 1a, an assumed effect size of *d* = .35 of the effect of PM_2.5_ on ADRD risk across burn seasons during the 3-year period was based on prior studies of cognitive decline and all-cause dementia in women related to PM_2.5_ [63]. Assuming 20 persons sampled per PM_2.5_ monitor area, this resulted in monitors covering 7 neighborhood block groups per community or N = 660 stratified across the 5 communities. For Aim 1b, effect size estimates for racial differences were based on findings of an approximately a twofold difference in hazard ratios of incident AD based on PM_2.5_ for non-Hispanic Black women compared to non-Hispanic White women or a difference in Cohen’s *d* = .45 [64] Assuming 20 persons sampled per PM_2.5_ monitor area, sample size estimates for power = .8 for the interaction of burn season by race, resulted in monitors covering at least 10 neighborhood block groups in each community for a total sample size of N = 1,000 stratified across the five communities. For Aim 2a, an assumed effect size of the built environment on cognitive function of *d* = .325 was based on Besser’s study finding of the relationship of proportion retail in 1/2-mile buffer to digit symbol coding as a measure of processing speed [65]. Assuming 20 persons sampled per neighborhood (census block), the sample size to detect an effect of the built environment on ADRD risk required six block groups per community for a total sample size of N = 600 stratified across five communities. Because Aim 1b provides the limiting sample size, the target sample size will be 1,000. Although there is a lack of literature to base the effect size for Aim 2b, the minimally detectable effect size with number of neighborhood block groups equal to 10 and n = 20 is *d* = .38. To account for 8% attrition [66–68], 1,087 participants will be recruited for the study. Conversions among risk measures and Cohen’s d were made in accordance with prior research and assumed a base rate = 0.107 of all-cause dementia [69]. Power analysis programs for mixed linear models, GLIMMPSE [70] CRT Shiny App [71] and PowerUp! [72] were used in these calculations.

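### Aim 1a's N = 660 does not equal 7 block groups × 5 communities × 20 people (700), and under the inputs printed the Aim 1a/2a and Aim 1b/2b sample-size figures are inverted

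*Protocol article*

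**What the plan says.** Everything is in one paragraph of the Protocol article, Sample size calculations for full sample. It opens with inputs that are not tied to any single aim: "Sample size estimates were made to attain .8 power for Aims 1 and 2", and "The intraclass correlation was assumed to be .05 based on the cluster of neighborhoods within rural communities". The cluster size is the same throughout. For Aims 1a and 1b the wording is "Assuming 20 persons sampled per PM_2.5_ monitor area", and for Aim 2a it is "Assuming 20 persons sampled per neighborhood (census block" group in effect, since the result is counted in block groups.

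The results by aim are:

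- Aim 1a, d = .35: "this resulted in monitors covering 7 neighborhood block groups per community or N = 660 stratified across the 5 communities".
- Aim 1b, d = .45, burn season by race interaction: at least 10 block groups in each community, N = 1,000.
- Aim 2a, d = .325: the calculation "required six block groups per community for a total sample size of N = 600 stratified across five communities".
- Aim 2b, no assumed effect: "the minimally detectable effect size with number of neighborhood block groups equal to 10 and n = 20" is given as d = .38.

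The study is then sized on one of these: "Because Aim 1b provides the limiting sample size, the target sample size will be 1,000". Allowing for 8% attrition, 1,087 are to be recruited.

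**The concern.** Two things look wrong. First, the Aim 1a total does not equal block groups × communities × people per block group, although the other two totals do. Second, with power, ICC and cluster size held fixed, a larger standardised effect of the same kind should need fewer people. The paragraph shows the reverse for the two main effects (1a against 2a) and for the two race/ethnicity interactions (1b against 2b).

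The second pair matters more. Aim 1b sets the study size, and the Aim 2b detectable effect is the only statement about what that size can show for effect modification by the built and social environment. A reader cannot tell which interaction figure to rely on.

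Aims 1a and 1b should not be set against each other in this way. An interaction can need more people than a main effect even when its d is larger.

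**Working it through.** **Inputs.** Power .80, ICC .05, 20 people per area, 5 communities, and the effect sizes and totals above, all from the power section. Alpha is not printed; I assume two-sided .05, so the multiplier is 1.960 + 0.842 = 2.802. A 1:1 contrast is also assumed.

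**1. Products**

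| Aim | Block groups × 5 × 20 | Printed N |
|---|---|---|
| 1a | 7 × 5 × 20 = 700 | 660 |
| 2a | 6 × 5 × 20 = 600 | 600 |
| 1b | 10 × 5 × 20 = 1,000 | 1,000 |

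660/20 = 33 areas, and 33/5 = 6.6 block groups per community. The gap is 40/660 = 6.1%. The attrition step reproduces: 1,000/0.92 = 1,087.

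**2. Main effects.** The design effect is 1 + (20 − 1) × .05 = 1.95. Multiply the individually sampled two-group N by it and round up to whole block groups per community (100 people each).

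- Aim 2a, d = .325: 298 × 1.95 = 581, or 5.81 per community, rounded up to 6. N = 600, as printed.
- Aim 1a, d = .35: 258 × 1.95 = 503, or 5.03 per community, rounded up to 6. N = 600, neither 660 nor 700.

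Scaling by 1/d² from the plan's own figures:

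- Aim 1a from Aim 2a: 600 × (.325/.35)² = 517.
- Aim 2a from Aim 1a: 660 × (.35/.325)² = 765, or 700 × (.35/.325)² = 812.

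A noncentral t calculation with (areas − 2) degrees of freedom gives 28 areas (560 people) for d = .35 and 32 areas (640) for d = .325. At d = .35, power is .877 with 33 areas and .896 with 35. This method misses the printed 600 for Aim 2a slightly (30 areas give power .786), but it orders the two aims the same way.

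**3. Race/ethnicity interactions.** Aims 1b and 2b are both analysed through cross-level interactions (Planned statistical analyses, Aim 1B and Aim 2B). Both are quoted at 10 block groups with 20 people each.

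- If d = .38 at 1,000 holds for both: Aim 1b needs 1,000 × (.38/.45)² = 713, and its power at 1,000 is Φ(2.802 × .45/.38 − 1.960) = Φ(1.36) = .91.
- If d = .45 at 1,000 holds for both: the Aim 2b detectable effect is .45, and power at .38 is Φ(2.802 × .38/.45 − 1.960) = Φ(0.41) = .66.

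**4. Can either interaction figure be right by itself?** Let Q be the share in one ethnoracial group, with 50 areas of 20 and an area-level 1:1 exposure contrast. The detectable effect is 2.802 × √[.95/(.25 × Q(1 − Q) × 1,000)] with a fixed slope; a random slope adds .05/(.25 × 50) under the root.

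- Q = .5: .345 (fixed) to .388 (random). The .38 is plausible.
- Q = .2: .432 to .467. The .45 is plausible.

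So each figure can be reached, but from different inputs, and the paragraph does not say that the inputs differ.

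**The case against.** The best defence is that the four calculations are not alike. The paragraph names three power programs. The Aim 1 effects concern burn seasons over three years and rest on conversions from risk measures, while the Aim 2a effect comes from an association with a cognitive score. Within-person correlation, ethnoracial split, alpha and covariate R² are not printed, and an article commonly leaves these to the full protocol.

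This can be made concrete. Suppose Aim 1 is a between-area contrast in change. Its variance relative to a cross-sectional contrast is multiplied by 2(1 − ρ). Comparing N × d²:

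- 1a/2a: (660 × .35²)/(600 × .325²) = 80.85/63.4 = 1.28, so ρ = .36.
- 1b/2b: (1,000 × .45²)/(1,000 × .38²) = 202.5/144.4 = 1.40, so ρ = .30.

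A single unstated correlation of about .30 to .36 would account for both inversions. That stands, and it limits the point to a conflict under the inputs printed. It also means that a reader who infers that repeated measures must make the mismatch worse goes too far: that is true of a purely within-person season contrast, but not of a between-area contrast in change when ρ is below .5.

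The 660 may also be an unrounded requirement of 33 areas printed beside a rounded-up count of 7. That is possible, but the text does not say so, and the other two totals are exact products.

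**Conclusion.** The point holds in limited form. The mismatch of 700 and 660 follows from the printed numbers alone. The two inversions hold under the one power, ICC and cluster size printed, with two-sided alpha .05 assumed for the power figures. They could disappear if the aims used different inputs that the article does not show. The consequence is that power for the race/ethnicity interactions cannot be read from the document: .91 against .80 for Aim 1b at d = .45, or .66 against .80 for Aim 2b at d = .38, depending on which figure is carried across.

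Two stronger readings are not supported. A reader might infer that .80 power cannot hold for all aims. It can: if .38 is right, Aim 1b has about .91 at 1,000, and Aims 1a and 2a are printed as needing fewer than 1,000. A reader might also infer that Aim 1b is not the limiting aim. Even its lowest figure here, 713, exceeds every figure for Aim 1a (503 to 700) and the printed 600 for Aim 2a, and Aim 2b has no assumed effect from which to set a size. The enrolment target is therefore not in question.

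**What to change.** 1. Replace 660 with 700 for Aim 1a, or state that 660 (33 areas) is the requirement before rounding up to 7 block groups per community.
2. Re-run Aims 1a, 1b, 2a and 2b and print for each the inputs that separate them: the contrast tested, alpha, number of measurements and within-person correlation, ethnoracial split and covariate R².
3. For each aim, restate the required N or detectable effect and the power at N = 1,000. In particular, make the Aim 1b and Aim 2b figures consistent, or state the input that makes them differ.
4. Keep 1,000 and 1,087, and the statement that Aim 1b is limiting, unless the re-run changes them.

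The cost is recalculation and a few lines of text. No participants, visits or procedures are added.

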#### Sample size calculations for subsample

For Aim 3, based on our prior observation of predictive correlations between smartwatch-derived behavior markers e.g. activity and clinical measures of CF i.e. MoCA) [73], we assume an effect size of clinical prediction from behavior markers of *d* = 0.52. Estimated effect size is adjusted to account for self-report error [74]. Momentary readings from a sample of N = 120 is large enough to calculate 99% power for hypothesis tests. In prior studies, we found that sample sizes smaller than these provided sufficient power to evaluate learning performance [75].

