#### Specific aims

Aim 1. Examine the contribution of particulate matter <2.5μm (PM_2.5_) exposures to social isolation and cognitive function (CF), through multilevel growth modeling.

Aim 1a. Examine baseline levels and growth trajectories of SI and CF associated with changes in PM_2.5_ during agricultural burn and non-burn seasons over a 36-month period, accounting for individual- and neighborhood- level characteristics.Aim 1b. Examine the effect modification of race/ethnicity on the relationship of PM_2.5_ on baseline levels and growth trajectories of SI and CF, accounting for individual- and neighborhood-level characteristics.

Aim 2. Determine the effects of the built environment (e.g., retail destinations, park space) and social environment (e.g., crime, SES) on SI and CF through linear mixed modeling.

Aim 2a. Examine SI and CF associated with the built and social environment over a 36-month period (baseline, and FY 1,2,3), controlling for individual- and other neighborhood-level characteristics.Aim 2b. Explore the effect modification of race/ethnicity on the relationship of the built and social environment with SI and CF, in view of their educational and social disadvantage.

Aim 3. Contextualize SI and CF among residents from different ethnoracial groups using EMA and sensor- derived behavior models during burn and non-burn seasons in a subsample of 120 ethnoracially diverse participants, stratified by Lake O communities.

Aim 3a. Examine residents’ momentary changes in behavioral markers, mood, and cognitive performance, associated with changes in air quality and the social and built environment.Aim 3b. Characterize differences among ethnoracial groups and between women and men in their momentary changes in behavioral markers, mood, and CF performance in response to changes in air quality and the social and built environment.

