#### Timeline of study assessments

For the 36-month study, at the baseline visit (T0), which occurs immediately after consent, individuals will provide data on sociodemographics, health history, and health behaviors. Participants will return to complete six-month follow-up visits for a total of seven visits (baseline and six follow-ups). During each follow-up visit (T1-T6), individuals will complete the cognitive and mini-physical performance assessments, biomarkers (e.g., blood pressure, BMI), and PROMIS measures targeting perceptions of social isolation, alcohol use, anxiety, depression, sleep problems, physical function, fatigue, ability to participate socially, and degree of pain interference with activities of daily living. The first participant was enrolled on January 20, 2024.

For the smartwatch sub-study, participants will wear an Apple Watch SE for 2 four-week periods, one during burn season and one during a non-burn period. Social isolation and cognitive function will be assessed during both the burn and non-burn seasons to identify potential changes in response to smoke-related air pollution (PM_2.5_). These outcomes are critical for understanding the health impacts of air pollution on cognitive and social well-being. Built and social environments (e.g., park spaces and ethnoracial composition) will be characterized at baseline and repeated if more current addresses or data become available during the study. Air quality monitoring will be continuous throughout the 36-month period. Table 1 shows the schedule of assessments and instrument collection by visit.

**Table 1 pone.0312660.t001:** Data collection schedule for 36-month study.

Data collected	T0^d^	T1 6 mo.	T2 12 mo.	T3 18 mo.	T4 24 mo.	T5 30 mo.	T6 36 mo.
ADRD assessment (MoCA v.8.1–8.3 and Cognigram)^a^		X	X	X	X	X	X
Sociodemographics^b^	X	X	X	X	X	X	X
Health conditions/behaviors^b^	X	X	X	X	X	X	X
Blood pressure, height, weight^a^		X	X	X	X	X	X
Mini Physical Performance Test (mini PPT)^a^		X		X		X	
Psychosocial measures (e.g., isolation)^b^		X	X	X	X	X	X
Anxiety, depression^b^		X	X	X	X	X	X
Sleep problems^b^		X	X	X	X	X	X
Physical function, fatigue, pain interference^b^		X	X	X	X	X	X
Ability to participate socially		X	X	X	X	X	X
Alcohol use^b^		X		X		X	
Air pollution monitors^c^	X	X	X	X	X	X	X

FU = Follow-up; mo = month; ^a^ From clinic assessment; ^b^ From questionnaire; ^c^ Monitors distributed at key sites within communities; ^d^ Screening visit

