#### Aims 3A and 3B

Random forests, convolutional neural networks, and gradient-boosted models will predict clinical measures and will be evaluated using leave-one-subject-out validation. Performance will be compared with mean and median baseline predictions for statistical significance. The primary analysis will model effects of activity level, social activity, and built environment averaged over burn season and year, although changes over time will also be assessed. Based on a continuous collection of over 8 weeks from 120 participants, we will collect at least 1.5 billion movement readings, 625,000 locations, 43,000 EMA responses, and 3,000 n-back scores. We will use the EMA responses, n-back scores, and ADRD risk scores as our target variables. The independent variables used to form the machine learning feature vectors will be daily digital behavior markers for each participant.

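### The blanket 99% power for Aim 3 is not supported for the person-level prediction effect it is based on; for that effect 120 people give about 79%

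*Protocol article*

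**What the plan says.** The section Sample size calculations for subsample starts from earlier correlations between smartwatch markers, such as activity, and clinical measures of cognition, with the MoCA as the example. It assumes an "effect size of clinical prediction from behavior markers of *d* = 0.52", says this value has been adjusted for self-report error, and concludes: "Momentary readings from a sample of N = 120 is large enough to calculate 99% power for hypothesis tests". For Aim 3 it gives no test, alpha, sidedness, number of readings or within-person correlation, and it does not restrict the 99% to any particular hypothesis.

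The hypotheses in question are of several kinds. Under Specific aims, Aim 3a concerns momentary changes as air quality and environment change, while Aim 3b is to "Characterize differences among ethnoracial groups and between women and men" in those changes. Under Aims 3A and 3B, machine-learning models predict clinical measures, are validated by leaving out one subject at a time, and are tested against mean and median baseline predictions. The targets there are EMA responses, n-back scores and ADRD risk scores.

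**The concern.** The effect size and the power statement appear to use different units. The effect is an association across people: a person's behavior markers against that person's clinical score. The power statement counts "Momentary readings from a sample of N = 120", as if the many readings per person added information about that association. They can make each person's marker more precise, but they leave 120 pairs of marker and clinical score.

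What is at stake is how a null result in Aim 3 would be read. At 99% power, an effect of the assumed size would be missed once in a hundred studies; at 79% it would be missed about once in five. An unrestricted 99% also covers the group comparisons of Aim 3b, where power depends on group sizes that are not given.

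**Working it through.** **Inputs.** From Sample size calculations for subsample: N = 120, d = 0.52, stated power 99%. The wear schedule, "participants will wear an Apple Watch SE for 2 four-week periods", gives 2 × 28 = 56 days. Assumed, because the article does not give them for Aim 3: alpha .05, two-sided (one-sided also shown), and the equal-split conversion from d to r. No further attenuation is applied, since d is said to be adjusted already.

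**Step 1. Can 99% be reproduced?** Yes, if 0.52 is given a meaning other than the one described.
- Paired or one-sample t-test with d in units of the within-person difference: noncentrality 0.52 × √120 = 5.70, power 99.99%.
- Burn versus non-burn difference with d in raw SD units: d_z = 0.52/√(2(1 − ρ)). For ρ = 0, .2, .5 and .7, d_z = 0.368, 0.411, 0.520 and 0.671, with power 97.9%, 99.4%, 99.99% and above 99.9%.
- Two sets of 120 independent readings: 98.1% two-sided, 99.1% one-sided. This counts 240 independent units where there are 120 people.
- Taking 0.52 as a correlation: above 99.9%. The article labels it d, not r.

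**Step 2. Power for the effect described.**
- r = d/√(d² + 4) = 0.52/√(0.2704 + 4) = 0.252.
- Fisher transform: atanh(0.252) = 0.257. Multiplied by √(120 − 3) = 10.82, this gives 2.78.
- Two-sided: Φ(2.78 − 1.96) = 79.4%.
- One-sided: Φ(2.78 − 1.645) = 87.2%.
- N for 99%, two-sided: ((1.960 + 2.326)/0.257)² + 3, about 281.
- N for 80%, same formula: 122. A sample of 120 is therefore close to what 80% power requires for this effect.

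**Step 3. Aim 3b, for illustration only.** The article gives neither group sizes nor a within-person correlation, so these are assumptions.

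| Comparison at d = 0.52, two-sided .05 | Power |
|---|---|
| 60 vs 60, each person counted once | 81% |
| 30 vs 90, each person counted once | 69% |
| 60 vs 60, 56 readings each, ICC 0.8 | 88.8% |
| 60 vs 60, 56 readings each, ICC 0.5 | 97.9% |
| 60 vs 60, 56 readings each, ICC 0.4 | 99.4% |

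The repeated-reading rows take d in units of the single-reading SD and multiply the variance by (1 + 55 × ICC)/56. At ICC 0.8 the factor is 45/56 = 0.804; at ICC 0.4 it is 23/56 = 0.411. Power for a group contrast thus runs from well below 99% to just above it, depending on two quantities that are not stated.

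**The case against.** The strongest defence is that 99% is not an arithmetic error at all. The text speaks of momentary readings, Aim 3a is about within-person change, two of the three kinds of target (EMA responses and n-back scores) repeat within person, and comparing a model with a baseline prediction on the same held-out subjects can be seen as paired. On a paired reading N = 120 and d = 0.52 do give over 99%, and the simple correlation test used in Step 2 is not named anywhere in the plan. Aim 3b, too, concerns group differences in momentary response, so a one-value-per-person t-test discards information.

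Much of this stands. A reader might infer that the 99% is simply wrong; the article does not support that, because the test is unnamed and a paired test reproduces the figure. Nor does it support a claim that every group comparison has less power than the prediction: an equal split by sex gives about 81% against 79%, and repeated readings can raise it.

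The defence fails on what d = 0.52 is. The section defines it as prediction of a clinical measure and derives it from marker–MoCA correlations. It does not present it as a burn versus non-burn difference or as a difference in prediction error, and it gives no reason for transferring the value to either.

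A reader might also infer that the yields under Aims 3A and 3B, "43,000 EMA responses, and 3,000 n-back scores", are impossible. With an app that "queries participants 4 times a day at random times during waking hours", there are 120 × 56 × 4 = 26,880 prompts, and 43,000 exceeds that only if one response means one answered prompt. Four items at each prompt plus two at the last make 18 a day, or 120 × 56 × 18 = 120,960 answers (96,768 at the 80% adherence target), so 43,000 is feasible. The n-back figure is given as a minimum, and 120 × 56 = 6,720 scheduled tests (5,376 at 80%) satisfy it. No error in the yields is established.

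**Conclusion.** The concern holds in limited form. For the effect that the article describes, power with 120 people is about 79% two-sided (87% one-sided), not 99%, and about 281 people would be needed for 99%. This rests on an alpha of .05, the equal-split conversion from d to r, and one clinical score per person.

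For a within-person contrast the 99% may be right, provided that 0.52 is a defensible effect size in the units of that contrast, which the article does not say. For the Aim 3b comparisons the figure is neither confirmed nor refuted: the inputs that would decide it are missing, and plausible values fall on both sides. The defect is one unrestricted figure attached to an effect size that does not yield it.

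**What to change.** In Sample size calculations for subsample:

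1. Name the test, alpha, sidedness and unit of analysis for each kind of Aim 3 hypothesis.
2. For prediction of a per-person clinical score, state power as about 80%, with the conversion from d to r shown.
3. Keep 99% only for a within-person contrast, such as burn versus non-burn, if that is what was meant. State d in the units of that contrast and why 0.52 applies to it.
4. Do not apply 99% to the Aim 3b comparisons of sexes and ethnoracial groups unless power is recomputed from the expected group sizes, number of readings and within-person correlation, with a range where these are uncertain.

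The change is to text and calculation only; sample size and data collection are unaffected. The cost is a less favourable stated power for the prediction analysis, and possibly for some group comparisons.
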